#### Data management

A Microsoft Access-based information system will be developed (Microsoft Access®, 2007). Data will then be stored on a secured server in the CIC-1433 EC (Centre d’Investigation Clinique − 1433 Epidémiologie Clinique) of the teaching hospital. To ensure the quality of the data collection, the independent data monitoring committee will execute a data quality control will be planned.

#### Data analysis

The analyses will be performed using SPSS and SAS software. Basic descriptive statistics, including means, standard deviations and frequencies will be calculated. A comparison of PA levels will be made across groups of patients depending on their hospital site and cancer localization. An identification of PA profiles and trajectories during the study will be conducted using a latent class growth analysis [47]. Relationships between the individual and interpersonal variables of the socio-ecological model will be tested using multilevel structural equation modeling. Profiles of PA practice among cancer patients will also be approached through the qualitative data collection, to identify further societal and policy factors, using Nvivo software.

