**Discussion:**

The present study aims to identify key levers and typical trajectories for PA practice among cancer patients, adapted to different times in the course of cancer and taking into account “what works”, “for whom”, “where” and “how”. The challenge is the tailoring of PA interventions to patients at different times in their cancer trajectory, and the implication of medical staff support.

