## Methods/design

The present study is designed as a mixed-method study using a sequential nested design QUAN (QUAL+QUAL) [28, 29]. The sequential design is based on a three-phase data collection process (see Table 1 for details), where qualitative data on medical staff will be collected before patient inclusion, followed by patient quantitative data collection lasting one year and a final qualitative data collection on a sample of patients one year after inclusion. The design will be nested because the three data collections will address different research questions, since the analysis of individual and interpersonal factors will be based on quantitative data and qualitative findings from medical staff, and patient data will complete the socio-ecological model for the social and policy environment. An interview guide will be used in the patient qualitative data collection, and the theoretical patient sampling for phase 3 will be informed by quantitative data from phase 2. The integration of the results will consist in the interpretation and explanation of the quantitative results, also making use of the qualitative results.

**Table 1 Tab1:** Description of the mixed method design

	Research question	Procedure	Data collection	Data analysis	Expected results	Data integration
Phase 1	What is observed among medical staff in terms of knowledge of and support for PA practice?	Case analysis per hospital	Interviews with health professionals using snowball sampling and document analysis	Content analysis using Nvivo software	Information on PA knowledge and support from medical staff, application of prescription requirements and orientation of patients to PA practice	Complete quantitative data on social support, public policies and organizational factors that encourage PA practice
Phase 2	What are the psychological and social factors influencing PA practice from cancer diagnosis to remission?	Cohort study on 680 patients included at diagnosis (T0; + 6 months; + 1 year)	Self-reported questionnaire	Descriptive, multivariate, multilevel analysis using SPSS, SAS and AMOS	Patient profiles for PA practice, theoretical model of interaction over time between social and psychological variables supporting PA practice	Quantitative data underpins the main data analysis Identification of patient profiles for the phase 3 study

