#### Sample size and sampling method

The principal judgment criterion is the compliance with PA recommendations (i.e. 150 min of at least moderate PA per week). In a previous cohort study [36], 15% of breast cancer patients (*n* = 466) managed to comply with these recommendations. Considering the fact that patients with factors facilitating PA practice are twice as likely to comply with these recommendations (Odds Ratio = 2), with an alpha risk of 5% and a power of 80%, 660 cancer patients will be included (220 per cancer localization). Taking into account a potential loss of 5% of the patients (11 patients per localization), we hope to include and follow a total of 693 patients (231 for each cancer localization). The data collection will last 12 months, reaching 30 patient inclusions per month in each hospital.

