Situational variables will include passion [41], satisfaction of basic needs in sport [42], state-hope [38], self-determined motivation for PA [43], anxiety and depression [44]. The two dimensions of passion (harmonious and obsessive) will be measured on a 12-item scale [41], where answers will be rated on a 7-point Likert, ranging from 1 “totally disagree” to 7 “totally agree”. The basic needs satisfaction (autonomy, competence and relatedness) will be collected using a validated French scale in the sports context [42]. Participants will answer on a 7-point Likert scale, ranging from 1 “totally wrong” to 7 “totally true”. The Adult dispositional Hope scale [38] will be used to explore state-hope. This scale includes 6 items (2 dimensions: operational and motivational components), and will be answered on a 6-point Likert scale, ranging from 1 “totally disagree” to 6 “totally agree”. All six dimensions of self-determined motivation for PA [43] will be explored using an 18-item scale, with a 6-point Likert response scale ranging from 1 “does not correspond at all” to 6 “corresponds totally”. The Health Anxiety Depression Scale, adapted into French [44] will measure anxiety (7 items) and depression (7 items), on a three-point scale.

Physical activity and sedentary behaviors will be measured using the self-reported Global Physical Activity questionnaire [45]. This questionnaire will measure the frequency, intensity, and duration of PA practice, as well as its context (work, mobility or leisure). PA preferences will also be evaluated in terms of type of practice, duration, intensity etc. [46].

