#### Data collection

The inclusion of patients will be conducted by oncologists at the first visit to the oncology department (see Fig. 2 for patient flow diagram). The study will be presented verbally to patients that meet the inclusion criteria. Patients will give their verbal consent to participate in the study, and if they agree to participate, the oncologist will contact the clinical research assistant to administer the baseline (T0) survey to the patients. The patients will be allowed to answer the questionnaire directly or to take it home and return it within a month to the research center. The T1 and T2 visits will be integrated into the patients’ clinical follow-up. The clinical research assistant will call a few days before the visit to the oncology department to remind them to plan for a further 20 min during their visit to fill in the questionnaire. Once again, if the patients wish, they will be allowed to take the questionnaire home and return it within a month to the research center. A reminder will be send after 2 weeks. Thirty patients will be contacted at T2 to participate in an interview on a voluntary basis (for phase 3), depending on their PA practice and characteristics.

The questionnaire will be filled in three times by the cancer patients: at diagnosis (T0), six months after diagnosis (T1) and one year (T2) after diagnosis. At each time, patients will respond to the questionnaire on physical activity, preferences and situational variables. At T0, patients will also provide information on medical, socio-economic and personality variables. At T2, patients will also provide information on personality variables, to address the stability of these characteristics among individuals facing such an important event as cancer.

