### Integration of qualitative and quantitative data

The nested mixed method design will help to address three different questions, but the quantitative data will be the grounding for the integration of the data, whilst the qualitative data will help to provide insight into interpersonal, societal and policy factors influencing PA practice. Phase 2 data will be crossed with phase 1, to identify patient counseling and the PA offer that best supports their PA level at the different times d in the course of the cancer. Phase 2 data will help to identify phase-3 participants, through an analysis of PA trajectories, and the crossing of the two data-sets will provide a picture of the factors to take into account to calibrate a PA intervention for cancer patients based on the socio-ecological model.

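### Latent class growth analysis will usually return several classes when patients differ only in activity level, so the class count does not show distinct trajectories

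*Protocol article*

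**What the plan says.** The Data analysis section of Phase 2 in the protocol article gives one quantitative method for this purpose: "An identification of PA profiles and trajectories during the study will be conducted using a latent class growth analysis". The same section assigns multilevel structural equation modelling to relationships between variables. It also adds a second, non-quantitative route: "Profiles of PA practice among cancer patients will also be approached through the qualitative data collection".

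Trajectories are a declared product of the study. The Discussion paragraph of the abstract states: "The present study aims to identify key levers and typical trajectories for PA practice among cancer patients". Table 1 lists among the expected results of Phase 2: "Patient profiles for PA practice, theoretical model of interaction over time between social and psychological variables supporting PA practice". They are also used later, in the section on integrating the two kinds of data: "Phase 2 data will help to identify phase-3 participants, through an analysis of PA trajectories".

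PA comes from the "self-reported Global Physical Activity questionnaire" and is collected "at diagnosis (T0), six months after diagnosis (T1) and one year (T2) after diagnosis", so each patient contributes at most three values.

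**The concern.** Latent class growth analysis sets the between-patient variance within each class to zero. Its one-class model therefore says more than that there is a single trajectory: it also says that a patient's three PA values are uncorrelated. If some patients are simply always more active than others, that model is wrong, and the method can absorb the difference only by adding classes. One continuous population is then cut into parallel low, middle and high bands.

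If those bands are reported as typical trajectories, differences in level would be read as different courses from diagnosis to remission. The first specific objective concerns how PA evolves, so this would bear directly on its answer. Neither of the other analyses in the section tests the existence of classes. The structural equation model addresses relationships between variables. The interviewees are themselves chosen by their PA profile (Phase 3, Data collection), so their accounts cannot independently confirm it.

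**Working it through.** **1. The plan's own figure.** The article gives no figure for the number of classes. Its sample size answers another question, compliance with PA recommendations: "with an alpha risk of 5% and a power of 80%, 660 cancer patients will be included (220 per cancer localization". From 15% and an odds ratio of 2, the odds are 0.15/0.85 = 0.1765, doubled 0.3529, giving 0.3529/1.3529 = 26.1%. With two-sided 5% (assumed) and 80% power, this needs 208 per exposure group, or 225 with continuity correction; the stated 220 lies between. The article applies 220 to each cancer localization, a separate matter that does not affect this point. The allowance for loss reproduces: 220 × 1.05 = 231 and 660 × 1.05 = 693. The simulations use n = 660.

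**2. The model.** Suppose all patients share one trajectory and differ only in level: y(i,t) = μ(t) + b(i) + e(i,t), with ICC = Var(b) / [Var(b) + Var(e)]. Two values from one patient then have covariance Var(b). Latent class growth analysis has no b(i). Its implied covariance between waves s and t is Σ π(k)[μ(k,t) − μ(t)][μ(k,s) − μ(s)], which is zero with one class. Any positive ICC can be fitted only through K ≥ 2.

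**3. Inputs.** From the article: 660 patients and three waves. Assumed, because the article does not give them: ICC (shown as a range), choice of K by lowest BIC, and a common dip-and-recover trajectory (for example 0, −0.4, −0.1 SD). Simulation A used 40 runs per setting and up to 4 classes. Simulation B was programmed separately, with 100 runs, up to 5 classes for continuous PA and up to 2 for yes/no compliance.

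**4. Share of runs with two or more classes when there is one true trajectory.**

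| ICC | A, near-normal | B, near-normal | B, yes/no compliance |
|---|---|---|---|
| 0 | 0% | 0% | 0% |
| 0.1 | 17% | 32% | 2% |
| 0.2 | 100% | 100% | not run |
| 0.3 | 100% | 100% | 92% |
| 0.5 | 100% | 100% | 100% |
| 0.7 | 100% | 100% | not run |

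A further check with 15 runs per setting gave 3/15 at a within-patient correlation of 0.1 and 15/15 at 0.3 or more. Barring classes with under 5% of patients left the near-normal result at 100% for ICC 0.2 or more.

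**5. What the classes look like.** A three-class fit to 6,600 simulated patients with one true trajectory gave:

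| Share | T0 | T1 | T2 | Change T0 to T1 | Change T1 to T2 |
|---|---|---|---|---|---|
| 20% | −1.06 | −1.45 | −1.17 | −0.39 | +0.28 |
| 58% | 0.00 | −0.39 | −0.09 | −0.39 | +0.30 |
| 22% | 0.99 | 0.66 | 0.91 | −0.33 | +0.25 |

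The true changes were −0.4 and +0.3. All three classes follow essentially the same course at different heights.

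**6. A one-class comparator.** On the near-normal scale, a one-class random-intercept growth model beat the best latent class growth model (up to 4 classes) in all 40 runs at ICC 0.3 and all 40 at ICC 0.5, by a mean of 32 and 58 BIC points. Over other correlation structures with one true trajectory it won 15/15 runs in every setting except random-slope variance 0.3, where it won 11/15. When two shapes truly existed it won 0/15, so it did not suppress real trajectories. In simulation A's two-shape case (30% of patients with a sustained drop), latent class growth analysis chose 3 or 4 classes in every run instead of 2.

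**7. Scale.** On raw right-skewed PA, latent class growth analysis split the single population in 100% of runs at ICC 0, 0.3 and 0.5. It also beat the one-class random-intercept model, by a mean of 888 BIC points (ICC 0.3) and 819 (ICC 0.5). The comparator therefore works only if the distribution is suited to the data.

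**8. Swapping in a random-intercept growth mixture model.** With one true trajectory and a random intercept only, this model chose one class in 40/40 runs. Other structures broke it (20 runs each): autoregressive correlation 0.3, 0.4, 0.5 and 0.7 gave false splits in 6, 14, 20 and 20 runs; random-slope variance 0.1, 0.2 and 0.3 gave 4, 19 and 20; log(minutes + 1) with about 10% or 20% zeros at baseline gave 20/20. The false classes can differ in shape: one example was 0.33/−0.43/−0.41 against −0.30/−0.35/0.29.

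**The case against.** The strongest reply has four parts.

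- **Missing detail is not an error.** The article condenses a fuller protocol, and an analysis plan may exist. The rule for the number of classes, the PA scale and comparator models are commonly settled there. This stands, and their absence is not the complaint. The point rests on the model the article does name; choosing K by BIC within that family does not repair its one-class reference.
- **Level groups are legitimate profiles.** The section seeks profiles as well as trajectories, and states no hypothesis that distinct shapes exist. This also stands: low, middle and high groups are adequate for choosing 30 interviewees. It does not support calling them trajectories.
- **The downstream harm is limited.** Calibration of interventions draws on interviews and on crossing the datasets, not on the classes alone. The principal criterion and the sample size do not depend on this analysis. That is right, and it bounds the importance of the point.
- **The obvious replacement also over-extracts.** Step 8 confirms this.

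A reader might infer that the profile finding can never come out negative. The results do not support that: one class was always returned at ICC 0 on a near-normal or yes/no scale, and in most runs at 0.1. A reader might also infer that profiles rest on this analysis alone. The article states a qualitative route too, so it is only the sole quantitative method, although the qualitative route does not test whether classes exist.

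**Conclusion.** The point holds in a limited form. With the named model, several classes are the usual result when patients differ only in PA level around one trajectory: 100% of runs at ICC 0.2 or more on a near-normal scale, and 92% to 100% at ICC 0.3 to 0.5 for yes/no compliance. The exception is very weak between-patient differences. The article itself studies traits and social conditions expected to make some patients more active than others, so an ICC near zero is unlikely, but no value is given. The class count is therefore not evidence of distinct trajectories.

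These figures assume 660 analysed patients, three complete waves, BIC selection and the simulated distributions. The point concerns what may be concluded about trajectories. It does not invalidate the grouping as description, and it does not show that a random-intercept mixture should replace it. It should be settled before the Phase 2 analysis.

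**What to change.** In the Phase 2 Data analysis section:

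1. Keep the latent class growth analysis and describe it as a descriptive grouping.
2. Add as a BIC comparator a one-class growth model with between-patient random effects or an unstructured within-patient covariance. With three waves, the unstructured form has 3 means and 6 covariance parameters and covers the random-slope case in which the random-intercept comparator was weakest. That form was not itself simulated.
3. Fit both with a distribution suited to skewed PA with zeros, such as a two-part or censored model. Neither raw minutes nor log(minutes + 1) with many zeros is reliable.
4. Report distinct trajectories only if the multi-class model beats the comparator and the classes differ in shape from T0 to T2. Otherwise report one average trajectory with between-patient variation and call the groups PA-level profiles. They remain usable for choosing Phase 3 patients.
5. If a random-intercept growth mixture model is wanted, make it a sensitivity analysis.

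The cost is analysis text and modest programming, with no new patients or data. The study may have to report that no distinct trajectories were found.

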### Phase 3: retrospective patient study

#### Sampling method

At T2, 30 patients will be recruited to participate in a retrospective personal narrative interview [48] on their PA practice since the cancer diagnosis. The objective will be to analyze societal and political levers for PA practice, as well as to explore the results for the variables collected (especially PA level and preferences) at T0 and T1. These interviews will also help to calibrate future interventions, on the basis of unexpected or non-measured variables detected within phases 1 and 2.

#### Data collection

An adapted retrospective interview procedure [48] will be used to collect PA involvement and various levers, from policies to individual factors, since the cancer diagnosis. As participants will be selected on the basis of their PA profile, retrospective interviews will help to refine their PA preferences, as well as to get a more complete picture of the socio-ecological model. Participants will be asked to identify the type and frequency of PA they engaged in before the diagnosis, at diagnosis, during treatment and after treatment, and which factors played a role in this engagement.

#### Data analysis

Interviews will be fully transcribed, and inductive thematic analyses will be conducted to identify the factors playing a role in PA practices and preferences, using Nvivo software.

### Integration of qualitative and quantitative data

The nested mixed method design will help to address three different questions, but the quantitative data will be the grounding for the integration of the data, whilst the qualitative data will help to provide insight into interpersonal, societal and policy factors influencing PA practice. Phase 2 data will be crossed with phase 1, to identify patient counseling and the PA offer that best supports their PA level at the different times d in the course of the cancer. Phase 2 data will help to identify phase-3 participants, through an analysis of PA trajectories, and the crossing of the two data-sets will provide a picture of the factors to take into account to calibrate a PA intervention for cancer patients based on the socio-ecological model.

## Discussion

Improving PA interventions for patients throughout their cancer trajectory is a major challenge, as the benefits of PA have been demonstrated in numerous studies [3, 4]. The present mixed-method protocol will identify factors at different levels and will cross theoretical models to produce robust data and key levers to calibrate these interventions. The collection of both qualitative and quantitative data will enable better coverage of the plurality of determinants of PA practice [11] and identify PA preferences and the interactions of its determinants at different times, from cancer diagnosis to remission. Studies exploring the habits of both healthcare professionals and patients in PA are rare, and evidence is needed to identify “what works”, “for whom”, “where” and “how” [24]. The study findings will help address this question and support the development of future interventions.

## Data Availability

Not applicable.

## Abbreviations

CIC-1433 EC: Centre d’Investigation Clinique − 1433 Epidémiologie Clinique
CNIL: French National Commission for individual privacy
ICL: Lorraine Cancer Institute
LOT-R: Life Orientation Test-Revised
PA: Physical activity
